**Table 4 Study groups**

| Treatment name          | Vaccine/Product name | Study groups |     |                      |
|-------------------------|----------------------|--------------|-----|----------------------|
|                         |                      | RRR          | ARR | Infectivity controls |
| Ad35.CS.01              | Ad35.CS.01           |              | x   |                      |
| RTS,S/AS01 B | RTS,S                | x            | x   |                      |
|                         | AS01 B    | x            | x   |                      |

- Treatment allocation: randomised (1:1).
- Blinding: observer-blind as to immunization regimens (see [Table 5](#)).

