### 10.4. Estimated sample size

For the final analysis, the target enrollment for this study will be 168 volunteers to ensure 69 subjects per study groups will undergo sporozoite challenge, given an approximate 20% estimated drop-out rate, based on past experience.

For the primary endpoint, the study will have 82% power to demonstrate an increase of 50% efficacy (2-sided Fisher exact test,  $\alpha=5\%$ ) of the ARR group over the RRR group, assuming a 50% attack rate in the RRR group. The increase in VE of the ARR group over the RRR alone group is defined as  $100 \times (1 - \text{AR}_{\text{Ad35.CS}} / \text{AR}_{\text{RTS,S}})$  where AR is the attack rate in the 2 groups.

The trial will have 80% power (2-sided Fisher exact test,  $\alpha=5\%$ ) to detect the following fold increase in AE rates of the ARR group over the RRR group (right column), depending on the rate of AEs in the RRR group (left column) (see [Table 30](#)).

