##### **10.8.2. Analysis of efficacy**

Efficacy will be assessed on the ATP cohort for efficacy by comparison of malaria incidence and time to onset of parasitemia after sporozoite challenge. Vaccine efficacy is defined as  $100 \times (1 - \text{Relative Risk})$ . Fisher's Exact test will be used for the comparison of malaria incidence between the two vaccinated groups. Kaplan-Meier analysis will be performed on time to onset of parasitemia, with testing between the two treatment groups using the log-rank statistic. Relative risk of infection and 95% confidence intervals (95% CI) will be calculated. All statistical tests will be two-tailed at 5% significance level.

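### Fisher's exact test is valid for the primary comparison but conservative; Boschloo's exact unconditional test gains 3.6 points of power at 69 per arm, less if the arms are unequal

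*Protocol*

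**What the plan says.** Section 10.8.2 names the test of the primary efficacy endpoint: Fisher's "Exact test will be used for the comparison of malaria incidence between the two vaccinated groups". The same paragraph adds: "All statistical tests will be two-tailed at 5% significance level". Section 10.4 plans on that test: "the study will have 82% power to demonstrate an increase of 50% efficacy (2-sided Fisher exact test", "assuming a 50% attack rate in the RRR group". It sizes the trial "to ensure 69 subjects per study groups will undergo sporozoite challenge", "given an approximate 20% estimated drop-out rate, based on past experience".

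The analysis is on the ATP cohort for efficacy. Under section 10.5.2 this requires all vaccinations within the protocol intervals, challenge, and available efficacy data. Section 10.8 leaves further detail to the statistical analysis plan, but the protocol itself fixes the test. It does not mention how conservative the test is.

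**The concern.** Fisher's test conditions on both margins of the two-by-two table: the group sizes and the total number infected. In this trial the total infected is not fixed in advance, so a valid test need not condition on it. Conditioning leaves few attainable p-values, so the test cannot use all of the 5% it is allowed.

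Boschloo's test takes the Fisher p-value as its statistic. It rejects at the largest cut-off that keeps the type I error at or below 5% for every common attack rate. Fisher's own size is below 5%, so that cut-off is never under 0.05, and Boschloo rejects whenever Fisher does.

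What is at stake is a few points of power in a trial whose size is hard to raise. Each cohort is capped at 46 challenged vaccinees (section 3), so three cohorts give at most 3 × 46 = 138, exactly the planned number. Section 9.2 says that withdrawals are not replaced.

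**Working it through.** **Inputs.** From section 10.4: 69 challenged per arm, attack rate 50% in RRR, 50% relative reduction, two-sided 5%. "The increase in VE of the ARR group over the RRR alone group is defined as" 100 × (1 − the ratio of attack rates), so the ARR attack rate is 50% × (1 − 0.50) = 25%.

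**Formulas.** Let b(x; n, π) be the binomial probability of x infections among n.
- Power = sum of b(x; n₁, 0.50) × b(y; n₂, 0.25) over the outcomes (x, y) that reject.
- Size = maximum over a common rate π of the sum of b(x; n₁, π) × b(y; n₂, π) over the same outcomes.
- Fisher rejects if its two-sided p ≤ 0.05. Boschloo rejects if Fisher's p ≤ c, with c the largest cut-off whose size is at most 5%.

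**The plan's own figure.** I enumerated all 70 × 70 = 4,900 outcomes at 69 per arm. Fisher's power is 82.35%, which reproduces the stated 82%. Its size is at most 3.36% (at π about 0.32). It is 3.29% at π = 0.25, 3.20% at 0.375 and 3.30% at 0.50.

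**Boschloo at 69 per arm.** The cut-off is c = 0.0688, with maximum size 4.98%. The next attainable cut-off, 0.0719, gives 5.01% and is not allowed. Boschloo rejects on 96 more outcomes than Fisher. Power is 85.95%, and 85.95 − 82.35 = 3.60 points.

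**Other attack rates**, same 50% reduction, 69 per arm:

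| RRR attack rate | Fisher power % | Boschloo power % | Gain (points) |
|---|---|---|---|
| 40% | 67.8 | 73.0 | 5.2 |
| 45% | 75.8 | 80.0 | 4.2 |
| 55% | 88.1 | 91.1 | 3.0 |
| 60% | 92.9 | 94.9 | 2.1 |

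**Unequal arms**, 50% vs 25% (π on a 999-point grid; gains taken from unrounded values):

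| RRR/ARR | Fisher max. size % | Fisher power % | Boschloo power % | Gain (points) |
|---|---|---|---|---|
| 69/69 | 3.36 | 82.35 | 85.95 | 3.60 |
| 69/68 | 4.12 | 83.65 | 85.80 | 2.15 |
| 68/69 | 4.12 | 84.53 | 86.67 | 2.13 |
| 67/66 | 4.13 | 82.87 | 84.59 | 1.73 |
| 67/64 | 4.24 | 82.29 | 83.20 | 0.91 |
| 66/63 | 4.20 | 81.95 | 82.32 | 0.37 |
| 62/66 | 4.28 | 82.71 | 83.04 | 0.33 |

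The pairs are examples, so read the range as approximate. For instance, the same enumeration at 66/69 gives a maximum size of 4.0% and a gain of 2.5 points. Boschloo's maximum size is at or below 5% in every pair.

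The drop at one subject's difference has a simple cause. With equal arms the conditional distribution is symmetric, so outcomes tie in pairs and the p-values move in larger steps. A small imbalance breaks the ties, and Fisher then uses more of its 5%.

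**With the futility rule.** If the Cohort A rule (23 per arm, stop if the estimated increase is 0% or less) is treated as binding, power at 69 per arm is 80.5% for Fisher and 83.7% for Boschloo, a gain of 3.3 points from unrounded values.

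**The case against.** The strongest objection is that nothing here is wrong. Fisher's test controls type I error, sections 10.4 and 10.8.2 name the same test, and the stated 82% already includes the conservatism. The design target of 80% (section 1.2.2) is met. All of that stands. A reader might infer from the 3.4% that the trial is underpowered or the analysis invalid, and the protocol supports neither.

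A reader might also take the 3.4% and the 3.6 points as general properties of this trial. They hold only for exactly equal arms at the planning rates. Section 3 asks for challenge numbers balanced by group. But 46 per cohort is a maximum, pregnancy or illness can prevent challenge (section 5.4.3.1), and section 10.5.2 removes subjects individually. A 20% loss taken exactly gives 168 × 0.80 = 134.4 challenged, about 67 per arm, so small departures from 69/69 lie within the plan's own figures.

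A third tempting inference is that the gain more than pays for a shortfall in challenged subjects. Comparing 69/69 with 66/66 suggests it: Fisher falls from 82.3% to 81.3%, while Boschloo gives 85.0% at 66/66. But Fisher's power is 82.9% at 67/66, 83.8% at 66/67, 84.2% at 68/66 and 82.4% at 66/68. A shortfall of that order need not cost Fisher any power, so the comparison is not robust and should not be used as an argument.

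Finally, Fisher's test can be justified by the random assignment alone, whereas Boschloo's 5% bound assumes one common attack rate, and these data are pooled over three cohorts. The difference in justification is real. The practical worry is not borne out: with attack rates allowed to differ across three cohorts of 23 per arm under the null, the Boschloo cut-off never exceeded 4.98%.

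**Conclusion.** The point holds as an optional improvement. At 69 per arm and 50% vs 25%, Boschloo's test has 3.6 points more power than Fisher's within the same 5% limit. With arms that differ by one to four subjects, the gain is about 0.3 to 2.2 points in the pairs tabulated, and Fisher's maximum size is then about 4.1 to 4.3%. The gain is never negative, because Boschloo rejects whenever Fisher does.

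These figures rest on the section 10.4 attack rates, binomial outcomes within each arm and, for the main comparison, no binding futility stop. The gain is larger if the RRR attack rate is below 50% and smaller if it is above.

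**What to change.** - In 10.8.2, name Boschloo's exact unconditional test, two-sided at 5%, as the test of the primary efficacy endpoint. State that its statistic is the two-sided Fisher p-value.
- Keep Fisher's exact p-value as a sensitivity analysis.
- In 10.4, quote the power of the named test and show how it changes with arm balance, for example at 69/69, 67/66 and 66/63.
- Make the change before any unblinded efficacy result exists, including the Cohort A interim (sections 5.4.4.2 and 10.7.2), so that the choice of test cannot be linked to the data.

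The cost is wording and standard software, with no extra volunteers. The downside is a less familiar test whose p-value needs maximisation over the common attack rate. If the sponsor prefers to keep Fisher's test, the plan remains valid as written.

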##### **10.8.3. Analysis of immunogenicity**

Immunogenicity analysis will be performed on the ATP cohort for analysis of immunogenicity.

Descriptive statistics and between group p-values will be calculated for all immunological read-outs.

##### ***Anti-CS, anti-Ad35 and anti-HBs antibody responses***

For each study group, at each time point that a blood sample result is available:

- Seropositivity rates for CS, Ad35 (with exact 95% CI) will be calculated by group.

- Seroprotection rates for HBs (with exact 95% CI) will be calculated by group.
- GMTs with 95% CI will be tabulated for antibodies for each antigen by group.
- The distribution of antibody titers for each antigen will be displayed using tables and/or reverse cumulative distribution curves.

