#### **1.1.2. CS-expressing recombinant human adenovirus 35 vaccine**

Adenoviruses, one of the common causes of upper respiratory and gastrointestinal infections, have been extensively studied in clinical trials and were one of the first gene

therapy vectors. Recombinant adenoviruses disabled by deletion of the early E1 genes are replication-deficient. As adenoviruses can directly infect dendritic cells, they promise to provide robust antibody and T cell responses to heterologous inserted and expressed genes.

Recombinant human adenovirus vaccine vectors, especially those using adenovirus serotype 5 (Ad5), have shown in pre-clinical and clinical Phase I studies to elicit potent antigen-specific cellular immune responses [Graham, 2005; Catanzaro, 2006; Harro, 2009]. However, the high prevalence of pre-existing anti-Ad5 immunity in human populations, particularly in the developing world, is likely to reduce the immune response of a recombinant Ad5 vaccine [Vogels, 2003; Kostense, 2004]. Other adenovirus serotypes such as Ad35, associated with lower worldwide seroprevalence, are therefore likely to be more relevant for use as vaccine candidates for the developing world.

Crucell has generated a CS-expressing recombinant human adenovirus 35 (Ad35.CS.01) which has already been evaluated in pre-clinical studies in mice and non-human primates as a stand alone or in a homologous prime-boost regimen, and showed the capability of inducing CS-specific antibodies as well as potent T-cell responses [Stewart, 2007; Shott, 2008; Rodríguez, 2008]. The Ad35 vaccine vector produced in the E1-complementing PER.C6@cell line has E1 and E3 regions deleted and is replication-incompetent. Ad35.CS.01 incorporates the full length CS gene. The N-terminus region has a consensus sequence designed to cover various circulating polymorphisms. The C-terminus sequence resembles that in RTS,S (3D7-derived). There are 27 NANP repeats, a cluster of 3 NANPNVDP repeats, and 1 separate NVDP repeat into the CS protein. An Ad35.CS.01 prime- RTS,S/AS01 boost regimen in a preclinical non-human primate study showed enhanced immunogenicity when compared to either vaccine candidate given alone. In particular, the prime-boost regimen led to a significant enhancement of the vaccine specific CD4 T cell responses when compared to the 3x RTS,S/AS01 immunization regimen [Stewart, 2007]. This Ad35.CS.01 vaccine candidate from Crucell has recently been tested in a Phase I clinical study in the U.S.

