  - Acute disease is defined as the presence of a moderate or severe illness with or without fever. Subjects with a minor illness (such as mild diarrhoea, mild upper respiratory infection) without fever may be enrolled at the discretion of the investigator.
  - Fever is defined as temperature  $\geq 38.0^{\circ}\text{C}$  ( $100.4^{\circ}\text{F}$ ) on oral, axillary or tympanic setting. The preferred route for recording temperature in this study will be oral.
- Acute or chronic, clinically significant pulmonary, cardiovascular, hepatic or renal functional abnormality, as determined by physical examination or laboratory screening tests.
- Any abnormal baseline laboratory screening tests: ALT, AST, creatinine, hemoglobin, platelet count, total white blood cell count, out of normal range as defined in the protocol [Table 28](#). (Amended 09 June 2011)
- Evidence of increased cardiovascular disease risk, “moderate” or “high”, according to the NHANES I criteria (see [Appendix A](#)).

***Note: NHANES I criteria will be applied for all subjects including subjects aged 18-35 years old. (Amended 09 June 2011)***

- An abnormal baseline screening electrocardiogram (EKG), defined as one showing pathologic Q waves and significant ST-T wave changes; left ventricular hypertrophy; any non-sinus rhythm excluding isolated premature atrial contractions; right or left bundle branch block; or advanced (secondary or tertiary) A-V heart block.
- Hepatomegaly, right upper quadrant abdominal pain or tenderness.
- Personal history of autoimmune disease.
- Seropositive for hepatitis B surface antigen or Hepatitis C virus (antibodies to HCV).
- Pregnant or lactating female.
- Female who intends to become pregnant during the study or planning to discontinue contraceptive measures.
- Suspected or known current alcohol abuse.
- Chronic or active intravenous drug use.
- History of blood donation within 56 days preceding enrolment.
- Any other significant finding that in the opinion of the investigator would increase the risk of having an adverse outcome from participating in this study.

A list of criteria that may eliminate subjects from ATP analyses can be found in Sections [6.7.1](#), [6.8](#) and [10.5](#).

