## 5.7.4. Biological samples evaluation

### 5.7.4.1. Blood testing plan

**Table 20 Summary of blood sampling time points and laboratory assays**

| Blood sampling timepoint      |                    | Component                                                               | No. subjects*             | Priority ranking |
|-------------------------------|--------------------|-------------------------------------------------------------------------|---------------------------|------------------|
| Type of contact and timepoint | Sampling timepoint |                                                                         |                           |                  |
| Visit 1 (D-90 to -3)          | Pre(D-90 to -3)    | Safety analysis                                                  |                           |                  |
|                               |                    | Hemoglobin, WBC, PLT, ALT, AST, creatinine                              | 168(+12/18 ± ) | 1                |
|                               |                    | Additional screening parameters                                  |                           |                  |
|                               |                    | HIV, HCV, HBV                                                           | 168(+12/18 ± ) | 1                |
| Visit 2 (D-7 to -1)           | Pre(D-7 to -1)     | Investigational analysis                                         |                           |                  |
|                               |                    | Anti-CS (RT ™ ) antibodies                                   | 168                       | 1                |
|                               |                    | Anti-HBs antibodies                                                     | 168                       | 2                |
|                               |                    | Anti-Ad35 neutral. antibodies                                           | 168                       | 3                |
|                               |                    | Anti-CS (FL ** & specific peptides other than RT) antibodies | 168                       | 4                |
|                               |                    | Isotype and affinity of CS-specific antibodies                          | 168                       | 5                |

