#### **6.7.1. Medications/products that may lead to the elimination of a subject from ATP analyses**

The following criteria should be checked at each visit subsequent to the first vaccination visit. If any become applicable during the study, it will not require withdrawal of the subject from the study but may determine a subject's evaluability in the according-to-protocol (ATP) analysis. See Section 10.5 for definition of study cohorts to be evaluated.

- Use of any investigational or non-registered product (drug or vaccine) other than the study vaccines during the study period.
- Chronic administration (defined as more than 14 days) of immunosuppressants or other immune-modifying drugs during the study period. For corticosteroids, this will mean prednisone  $<20$  mg/kg/day, or equivalent. Inhaled and topical steroids are allowed.
- Administration of a vaccine not foreseen by the study protocol during the period starting from 7 days before each vaccination and ending 7 days after each vaccination.
- Administration of immunoglobulins and/or any blood products during the study period.
- Drug and alcohol abuse.

A detailed, comprehensive list of reasons for elimination from ATP analyses will be established at the time of data cleaning.

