## **10.6. Derived and transformed data**

### **Immunogenicity**

- The cut-off value is defined by the laboratory before the analysis and is described in Section [5.7.3](#).
- A seronegative subject is a subject whose titer is below the cut-off value.
  - Anti-CS repeat antibody titers < 0.5 EU/mL.
  - Anti-CS full-length and peptides antibody titers < 200
  - Anti-Ad35 antibody titers < 16 IC90.

- A seropositive subject is a subject whose titer is greater than or equal to the cut-off value for the following antigens:
  - Anti-CS repeat antibody titers  $\geq 0.5$  EU/mL.
  - Anti-CS full-length and peptides antibody titers  $\geq 200$
  - Anti-Ad35 antibody titers  $> 16$  IC90.
- A hepatitis B virus seroprotected subject is defined as a subject whose antibody titer is greater than or equal to the cut-off value for the following antigen:
  - Anti-HBs antibody titers  $\geq 10$  mIU/mL.
- The Geometric Mean Titers (GMTs) calculations are performed by taking the anti-log of the mean of the log titer transformations. Antibody titers below the cut-off of the assay will be given an arbitrary value of half the cut-off for the purpose of GMT calculation.
- Handling of missing data:

For a given subject and a given immunogenicity measurement, missing or non-evaluable measurements will not be replaced. Therefore, an analysis will exclude subjects with missing or non-evaluable measurements.

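### Post-dose anti-HBs and anti-Ad35 results pool subjects with and without antibody at baseline, so they do not isolate the response that the ARR regimen induces

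*Protocol*

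**What the plan says.** - **Objective (Section 2.2).** The secondary immunogenicity objectives concern the humoral and cellular response to hepatitis B, and the humoral response to adenovirus, induced by the ARR regimen (one Ad35.CS.01 dose, then two RTS,S/AS01B doses).
- **Entry (Section 4.4).** The hepatitis B criterion excludes subjects who are "Seropositive for hepatitis B surface antigen or Hepatitis C virus (antibodies to HCV". This is a test for surface antigen, not for anti-HBs antibody or past vaccination. For adenovirus, only prior receipt of an investigational vaccine excludes; natural Ad35 antibody does not.
- **Definition (Section 10.6).** "A hepatitis B virus seroprotected subject is defined as a subject whose antibody titer is greater than or equal to the cut-off value", which for anti-HBs is 10 mIU/mL. Ad35 seropositivity is likewise a status at a cut-off of 16. Neither definition refers to baseline or to a rise.
- **Analysis (Section 10.8.3).** The tables are made "For each study group, at each time point that a blood sample result is available". They include "Seroprotection rates for HBs (with exact 95% CI) will be calculated by group" and "Seropositivity rates for CS, Ad35 (with exact 95% CI) will be calculated by group", plus GMTs by group. Between-group p-values are planned for all immunological read-outs.
- **Baseline sample (Table 20).** Visit 2, before dose 1, includes "Anti-HBs antibodies" and anti-Ad35 neutralising antibodies in all 168 vaccinees.
- **Other vaccines (Section 6.7.1).** One listed reason for possible removal from ATP analyses is receiving "a vaccine not foreseen by the study protocol during the period starting from 7 days before each vaccination and ending 7 days after" a study dose. No listed criterion covers other vaccines outside those windows.

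**The concern.** RTS,S carries hepatitis B surface antigen, so an adult already immunised against hepatitis B can be above 10 mIU/mL before dose 1 and remain so at every later sample. That subject adds to the post-dose seroprotection rate whether or not the regimen did anything. The same holds for natural Ad35 antibody and the Ad35 seropositivity rate. Section 10.8.3 does not state that any post-dose summary or comparison uses the subject's own Visit 2 value.

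The stake is how the secondary immunogenicity results can be read. The ARR post-dose rate is not the induced rate that the objective asks about. A pooled GMT combines subjects starting from nothing with subjects who were already positive. The between-arm tests are diluted. A hepatitis B vaccine given during the study, outside the 7-day windows, would add further response that is not due to the study regimen.

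**Working it through.** **The plan's own figure.** The only nearby design figure is the 82% power for primary efficacy (Section 10.4). Exact enumeration of the two-sided Fisher test with 69 per group, 50% v 25% and alpha 5% gives 82.3%, so it reproduces. This point does not touch it.

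**What background does to a pooled rate.** Let p be the share at or above the cut-off at Visit 2, taken as equal in both arms and still above the cut-off later. Let s be the response rate in baseline-negative subjects. The documents give neither, so all values are assumptions.

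- Reported post-dose rate = p + (1-p)s.
- Excess over the induced rate = p(1-s).
- Reported difference between arms = (1-p)(s1 - s2).

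For anti-HBs, take s = 70% for the reported rate and excess, and 90% v 70% for the arm contrast. Power is exact two-sided Fisher at 69 per group. Both the test and the group size are illustrative choices, since the protocol does not name the test for these p-values.

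| p | Reported rate, s = 70% | Excess (points) | 90% v 70% becomes | Difference (points) | Power |
|---|---|---|---|---|---|
| 0% | 70% | 0 | 90 v 70 | 20 | 80.7% |
| 10% | 73% | 3 | 91 v 73 | 18 | 74.7% |
| 20% | 76% | 6 | 92 v 76 | 16 | 67.5% |
| 40% | 82% | 12 | 94 v 82 | 12 | 50.2% |
| 60% | 88% | 18 | 96 v 88 | 8 | 28.8% |

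Example at p = 40%: 0.40 + 0.60 × 0.70 = 0.82, and 0.60 × 20 = 12 points.

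Restricting the test to baseline-negative subjects recovers little of this power, because the denominator falls too. At p = 40%, 69 × 0.60 is about 41 per group, and 90% v 70% then has 54.9% power against 50.2% pooled. The gain from the split is a rate that answers the objective. Any gain in precision has to come from the baseline adjustment of the GMTs.

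**Ad35.** RRR never receives Ad35.CS.01 (Table 22), so apart from new natural exposure its rate is p. With p from 5% to 20% and s from 20% to 40%, RRR reads 5% to 20%. ARR reads from 0.05 + 0.95 × 0.20 = 24% to 0.20 + 0.80 × 0.40 = 52%.

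**Day 28.** ARR has received no surface antigen when the Day 28 sample represents its response to dose 1 (Tables 20 and 22). Anti-HBs seroprotection in ARR in that sample therefore cannot come from the regimen.

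**The vaccine window.** Doses fall on Days 0, 28 and 56. Seven days either side covers Days -7 to 7, 21 to 35 and 49 to 63. Days 8 to 20, 36 to 48 and everything after Day 63 are outside. Table 20 takes anti-HBs at Days 28, 56, 77, 105, 140 and 236, and HBs-specific T cells at Days 42, 77, 105, 140 and 236. A hepatitis B vaccine on Day 40 would precede both the Day 42 T-cell sample and the Day 56 antibody sample, with no listed vaccine criterion engaged.

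**The case against.** The case on the other side is substantial, and much of it stands.

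- A reader might infer that background immunity goes unreported. It does not: the tables are made at every time point with a result, Visit 2 is one of them, and so pre-vaccination rates and GMTs appear for each arm. What they cannot show is which subjects responded.
- A reader might infer that the protocol counts background as vaccine-induced. No text says so. The rates are status measures and the endpoint is titres at specified time points. The mismatch lies between those measures and the wording of the objective.
- A reader might infer a biased comparison. Allocation is randomised 1:1, so background is balanced on average and dilutes the contrast without tilting its direction. Nor does any stated objective compare two with three surface-antigen doses; the hepatitis B objective names ARR only.
- The Ad35 part is weaker. The remark that pre-existing immunity "is likely to reduce the immune response of a recombinant Ad5 vaccine" concerns Ad5, and Section 1.1.2 goes on to describe Ad35 as having lower seroprevalence. In the earlier Ad35.CS.01 study, anti-Ad35 antibodies elicited by the vaccine showed no sign of interfering with the anti-CS response. RRR is a concurrent background control.
- On other vaccines, Section 6.7.1 leaves a fuller elimination list to data cleaning, and Section 6.7.2 has such vaccines recorded from 30 days before dose 1 to 6 months after the last dose. A Day 40 case would be identifiable, and it is not established that the subject stays in the ATP cohort. But the rule would then be set after the data exist.
- Section 10.8 defers detail to the statistical analysis plan, and a baseline-serostatus table could properly sit there. Its absence is not an error in itself. The case for change is that the method already stated, pooled rates and GMTs with between-group p-values, has a better alternative using data already planned.

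**Conclusion.** The point holds as an improvement to the secondary immunogenicity analysis. The protocol admits subjects with pre-existing anti-HBs or anti-Ad35, shows that background per arm at Visit 2, and then plans post-dose summaries and tests that do not use it. Post-dose rates overstate the induced rate by p(1-s), and between-arm differences in rates are diluted by (1-p). The size depends on p, which is unknown. Under the assumptions above, the overstatement runs from 3 to 18 points as p goes from 10% to 60%. The calculation assumes equal p in both arms and that baseline-positive subjects stay above the cut-off.

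The documents do not support the stronger readings: that background is hidden, that it is labelled as vaccine response, or that the ARR-RRR comparison is biased in direction. Primary efficacy and its power are not affected.

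**What to change.** 1. **Section 10.8.3, anti-HBs.** Adjust between-group GMT comparisons for the Visit 2 log titre. Present post-dose seroprotection and GMTs by Visit 2 status (below 10 v 10 mIU/mL or more), and take the induced rate from baseline-negative subjects.
2. **Section 10.8.3, anti-Ad35.** Add a supportive table by baseline serostatus, with RRR as background control. Before using that split, settle a titre of exactly 16: Section 10.6 puts seronegative below 16 and seropositive above 16, although its lead-in says at or above the cut-off.
3. **Section 6.7.1.** Add that anti-HBs and HBs-specific T-cell results obtained after any non-study hepatitis B vaccine given from Visit 2 onward are excluded from the ATP immunogenicity analysis.

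No new sample or visit is needed. The cost is analysis wording, one added criterion and smaller denominators: of 84 per group, about 84 × 0.60 = 50 would be baseline-negative at p = 40%, and about 84 × 0.40 = 34 at p = 60%, before drop-out. One limit remains: a subject vaccinated in the past whose titre is now below 10 mIU/mL would still be classed as baseline-negative.
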